## Overview of the Program

### Description of intervention and settings

The IPiC-Health initiative is a three year project (January 2023-December 2025) that engages a variety of ambulatory and inpatient healthcare sites and providers in delivering SBIR for health promotion as a routine component of patient care. These sites provide care to patients with a variety of acute and chronic health issues, including rheumatological conditions, surgery, diabetes, pneumonia, asthma, cardiac diseases, trauma, and geriatrics. This initiative leverages the province-wide electronic (“Connect Care”) clinical information system to help integrate the SBIR actions and documentation sustainably into routine care. Screening involves using standardized screening questions to identify patients who use commercial tobacco, consume alcohol at levels that increase risk, or who participate in insufficient physical activity [28,29,30,31,32,33]. The brief intervention is a conversation that providers have with patients who have elevated risk on one or more of those modifiable risk factors. The brief conversation aims to educate patients about the health risks, identify patient readiness to consider a change in behaviour, and to encourage them to take action. Providers are then able to offer educational resources (e.g., a brochure containing QR codes/links to relevant websites) that provide behaviour change information and support. Providers can also refer patients to support services available in their community (e.g., Alberta Quits program for tobacco cessation) (Figure 1).

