## Methods

### The design and key features of implementation and evaluation

We employ implementation-effectiveness hybrid study using mixed-methods [26]. This includes quasi-experimental design for quantitative assessment of SBIR implementation (adoption/coverage of intervention) and effectiveness (patient behaviour change and health service use) outcomes. We use both quantitative and qualitative methods to evaluate the implementation processes and providers’ experience of integrating SBIR into their workflows and patients’ experience of the SBIR intervention and of health behaviour change. Each participating site participates in a 6-month pre-implementation period, followed by 15-month SBIR implementation research period. Patients are followed up at 1, 6, and 12 months after they receive the SBIR intervention (Figure 2). Clinical sites that had used Connect Care for at least 6 months prior to recruitment into this project, and where the team identified health promotion and disease prevention as a priority, and expressed interest in participating in the study were engaged to participate.

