**Figure 2 F2:**
[figure not shown]
Overview of Intervention Implementation Design.

During the 6-month pre-implementation period, our onsite research coordinators recruit a no-intervention (control/comparison) group of study participants and conduct risk factor screening on recruited patients using paper-based version of the same screening tools as those in Connect Care that will be used during SBIR implementation. These patients do not receive risk factor screening by clinical team members and are not offered brief intervention and referrals. The 15-month SBIR implementation serves as the intervention period of the study during which patients are recruited to participate in the intervention group. Note that all patients served by the participating clinics/units during the intervention period are *eligible* to receive the SBIR intervention, regardless of whether or not they agree to participate in the research study. Over the course of the 15 months intervention period, as the SBIR practice is increasingly embedded into routine care, we expect a growing proportion of the patients served by the participating clinical teams will receive SBIR. Enrolled research participants are followed up over the course of 12 months (1, only for intervention group, 6, and 12 months) for collection of behaviour change and health services utilization data. During the monitoring of participant recruitment, any control participants who had subsequent visits to intervention sites and received the intervention at that time were excluded from the study.

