Patient follow ups: Effectiveness of SBIR intervention	Patients’ behavior change status for both control and intervention patient groups	Intention to change behavior, awareness about the problem, commitment to action, uptake to referral programs, active modification of behavior (such as quit attempt, reduce/quit tobacco use, reduce/stop alcohol intake, and initiate/increase physical activity). Covariates for effectiveness outcomes: Sociodemographic/socioeconomic (such as age, sex, marital status, ethnicity, education, employment, income, rurality, immigration-related factors) and overall physical and mental health status.	Primary data collection from patients.	Follow-up telephone interview at six months of index hospitalization discharge/visit. Data collection tool will include the questionnaires guided by the Prochaska model of change process and the risk factor screening questions included in the Connect Care

Healthcare resource use	Hospital readmissions and emergency visits for both control and intervention patient groups	Hospital readmissions and emergency visits during the year after index hospitalization discharge /visit. Reasons/diagnosis for readmissions and emergency visits, and family physician/primary care visits within 1-year of discharge/visit and diagnoses/comorbidities at the time of recruitment to 1-year of index hospitalization discharge/visit.	Administrative health databases: Discharge Abstract Database, National Ambulatory Care Reporting System, and physician claim databases	Data from multiple databases will be accessed through Data and Analytics. and will be linked with the follow-up interviews using the personal health numbers.

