## Research plans for evaluation of intervention effectiveness outcomes

*Study design and participants:* We use a quasi-experimental study design (pre-post with a comparison group). The intervention group are patients from participating units during the SBIR implementation period who screen at increased risk on any of the three risk factors and received brief intervention and referral support. The comparison group are patients from the same units, during a 6-month pre-implementation period, identified as having increased risk on any of the three risk factors, but who do not receive the SBIR intervention.

Study inclusion criteria for the target patient population to be enrolled in the effectiveness study include: Adult patients (>18 years) who are residents of Alberta, have the ability to engage in the SBIR process and data collection, and are attending the participating sites during the study period. Research assistants enroll the eligible patients in the study after they provide informed consent. The patients with severe disease conditions (i.e., unconsciousness and end-stage care) or those with mental or cognitive incapacity are excluded.

*Outcome definition and measurement for both groups:* Key outcomes are patient behaviour change in relation to the modifiable risk factors and health care utilizations in the year after recruitment to the study. Measurement of patient’s behaviour changes involves: questions on patients’ intention to change behaviour, their uptake of referral services (for those who received referrals), and changes in risk level as measured using the same risk factor screening tools used during the SBIR intervention. We also ask patients about tobacco use reduction, tobacco quit attempts, seven- and 30-day tobacco abstinence. The data are being collected via telephone interviews at 6 months follow-up after the index clinic visit, or discharge from a hospital stay, during which the patient was recruited into the study. A sample of participating patients are also called at 1 month after their hospital/clinic visit to ask them about their experience of the SBIR intervention.

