Health care utilization measures include hospital readmissions and emergency visits within one year of the index discharge/visits. These outcomes are of particular importance to facilitate outcome comparisons with other studies as well as because they are important to provide cost-effectiveness assessments to support intervention spread/scale decisions by health system administrators. The health care utilization data will be obtained from linked administrative health databases accessed through the Department of Data and Analytics, the custodian of these routinely collected healthcare data (Table 1).

Data on potential confounding variables including sociodemographic and socioeconomic status for both groups are collected during the 6 months patient follow-up interviews. Diagnosis and comorbidity related variables will be obtained from the administrative health databases. A detailed data collection plan is shown in data collection matrix (Table 1).

*Sample size:* SBIR intervention can increase smoking quit rate at 6-months by 11% [40], reduce alcohol misuse rate at 5-months by 19% [41], and increase patients’ average daily physical activity level by 22% [42]. Based on sample size estimation in relation to tobacco use (with effect size of 11%), we will need a maximum of 1,000 patients in each group (a total sample of 2,000 for controlled and intervention groups) to detect the smallest difference, among all outcomes, between the groups (with a study power of 80% and alpha of 0.05). This is the maximum number needed since tobacco is the least prevalent condition and it will also have the smallest proportion of change in behaviour after intervention, among the three risk factors. We will recruit a total sample of 4,000 (2,000 sample for controlled group and 2,000 for intervention group) to account for the anticipated 50% loss to follow up or nonresponse rate. The expected dropout rate is determined based on our previous paper-based SBIR pilot study [22].

*Analysis:* We will use log-binomial regression models to estimate risk difference and relative risk (for health behaviour change outcomes), and Cox proportional competing risk regression models to estimate hazard rate difference and hazard ratio (for health care use outcomes), to compare outcomes between the two groups adjusting for confounders, such as reasons or diagnosis for visits/admissions, comorbidity, and socioeconomic status.

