## Expected Results and Applicability

Thus far 4 inpatient units and 4 ambulatory clinics in Calgary and Edmonton cities in Alberta have participated in this project. Among those, 1 inpatient unit and 4 ambulatory clinics have completed the 6 months control period and started the implementation of SBIR, and remaining units/clinics are in the 6 months control phase. We have recruited a total of 2015 patients as control research participants (i.e., medium or high-risk level on any of the three risk factors). Of those, 1000 have completed 6 months follow-up calls. A total of 447 patients have received SBIR support from the participating units/clinics, with 175 patients being intervention research participants (i.e., consented for follow up survey). Among those intervention research participants, 48 have completed 1 month follow up survey calls, 75 have completed 6 months follow up calls, and 23 have participated in in-depth qualitative interviews. Approximately 50% of patients are responding to follow-up efforts.

The research participants recruitment and data collection activities are undergoing and key learnings to date are as follows.

High screening uptake: Providers are consistently screening and documenting for the risk factors.Low brief intervention rates: Offering brief advice or engaging patients in conversations about behavior change remains relatively low.Low documentation of brief intervention: When brief interventions are provided, they are often not documented in the Connect Care system.Referral gaps: Referral pathways—particularly for physical activity and alcohol use—are unclear, and referral functionalities for these risk factors are not currently integrated into the Connect Care system.Facilitators of implementation: Implementation is supported by clinical champions, embedded project staff at implementation sites, and ongoing rapid assessment and feedback.Participant eligibility challenges: Many patients are ineligible for the intervention or study participation due to critical health conditions particularly in some high acute care settings. This indicates that careful consideration of the setting and patient acute is important when deciding whether to implement SBIR.Improved recruitment: Using both in-person and phone-call recruitment strategies has led to an increase in participant numbers.

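### Former controls can never become intervention participants, so the new/returning patient mix may differ between groups, and no attendance before enrolment is listed for collection or adjustment.

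*Protocol article*

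**What the plan says.** The timing is set in the section on design and key features: "Each participating site participates in a 6-month pre-implementation period, followed by 15-month SBIR implementation research period". The effectiveness section then defines the control group: "The comparison group are patients from the same units, during a 6-month pre-implementation period". The intervention group is drawn from those units during implementation and is limited to patients at increased risk who actually received brief intervention and referral support.

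The paragraph after Figure 2 adds a rule for controls who come back: "any control participants who had subsequent visits to intervention sites and received the intervention at that time were excluded from the study".

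On setting, the article reports: "Thus far 4 inpatient units and 4 ambulatory clinics in Calgary and Edmonton cities". Conditions treated are described as "including rheumatological conditions, surgery, diabetes, pneumonia, asthma, cardiac diseases, trauma, and geriatrics".

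On adjustment, the effectiveness analysis compares the groups "adjusting for confounders, such as reasons or diagnosis for visits/admissions, comorbidity, and socioeconomic status". Table 1 adds: "Covariates for effectiveness outcomes: Sociodemographic/socioeconomic (such as age, sex, marital status, ethnicity, education, employment, income, rurality, immigration-related factors", and also overall physical and mental health status. Its healthcare-use row covers readmissions, emergency visits and primary care visits in the year after the index discharge or visit, and diagnoses and comorbidities from recruitment to one year.

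**The concern.** Taken together, the entry rule and the exclusion rule leave a former control no route into the intervention group. To enter, the patient must receive SBIR; on receiving it, a former control is removed from the study. The intervention group is therefore drawn from the units' attenders minus everyone already enrolled as a control.

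In an inpatient unit treating trauma or pneumonia this may matter little. In a clinic following diabetes, rheumatological disease or asthma, many attenders in the later window may be the same people as in the earlier one. The groups can then differ in how many patients are new to the unit. New and long-standing patients may differ in disease stage, response to advice and expected health-care use, so both the behaviour and the utilization outcomes are exposed. A newly referred and a long-standing patient with the same diagnosis, comorbidity and socioeconomic status look alike to the named adjusters.

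**Working it through.** **The plan's own figures.** The article gives no figure on this point. Its recruitment target reproduces, 1,000/(1 - 0.5) = 2,000 per group, and is not affected.

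**What is not given.** The article reports no share of returning patients, visit interval, fraction of attenders enrolled, or new/returning split. The 2,015 controls recruited so far come from inpatient units and clinics together and have no denominator, so they do not show how far any clinic's attenders have been depleted.

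**Attendance model (all inputs assumed).** A unit has R = 1,000 regulars, each visiting every T months (T = 3, 6 or 12). New patients are a fraction f of control-window attenders (10% or 30%). A fraction e of attenders is enrolled as controls (10%, 30% or 60%). Half of new patients return (q = 0.5). A fraction s of returning controls receives SBIR and is excluded (0 or 50%). All regulars attend at least once in 15 months.

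- Returning attenders, control window: A = R × min(1, 6/T)
- New attenders, control window: N = A × f/(1 - f)
- New attenders, intervention window: 15/6 × N = 2.5N
- New share later, without the bar: 2.5N/(2.5N + R + qN)
- New share later, with the bar: 2.5N/(2.5N + R + qN - eA - eqN)
- New share, retained controls: N(1 - sq)/[N(1 - sq) + A(1 - s)]

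**Worked case: T = 6, f = 10%, e = 30%.** A = 1,000, N = 111.1 and 2.5N = 277.8.

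- Without the bar: 277.8/1,333.3 = 20.8%. The longer window alone moves the share from 10% to 20.8%.
- With the bar: 277.8/(1,333.3 - 300 - 16.7) = 27.3%.
- Retained controls: 10.0% if s = 0; 83.3/583.3 = 14.3% if s = 50%.
- Net difference: +17.3 or +13.0 points.

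**Worked case with the opposite sign: T = 12, f = 30%, e = 10%, s = 50%.** A = 500, N = 214.3 and 2.5N = 535.7.

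- With the bar: 535.7/(1,642.9 - 50 - 10.7) = 33.9%.
- Retained controls: 160.7/410.7 = 39.1%.
- Net difference: -5.3 points.

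**All 36 combinations, in percentage points of new-patient share:**

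| Quantity | Range |
|---|---|
| Effect of the bar alone, e = 10% | +0.6 to +2.6 |
| Effect of the bar alone, e = 30% | +1.9 to +8.9 |
| Effect of the bar alone, e = 60% | +4.4 to +21.9 |
| Net difference, visits every 3 or 6 months | +8.3 to +38.8 |
| Net difference, visits every 12 months | -5.3 to +11.9 |

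Four of the 36 are negative. All four have 12-month visits, half of returning controls excluded, and 10% or 30% enrolled.

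**From mix to outcome.** With no SBIR effect, the false difference is the difference in new-patient share times the outcome gap between new and returning patients. The documents give no such gap. Purely as an illustration, assumed quit rates of 15% (new) and 9% (returning) turn -5.3 and +38.8 points of mix into 0.06 × -5.3 = -0.3 and 0.06 × 38.8 = +2.3 points of quit rate. Both the size and the direction of that gap are assumptions.

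**The case against.** The strongest reply is that the adjuster list is introduced as examples, in a condensed article, so a missing item does not show that the analysis will omit it. That stands as far as the list goes. It does not cover the data request: Table 1, which the article calls its detailed data collection plan, places administrative data only from recruitment forward. A variable that is not extracted cannot be added to a model later.

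Second, Table 1's health status and diagnoses partly stand in for disease stage and expected use. That is fair, but they do not record whether a patient is new to the unit.

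Third, a reader might infer that the control phase uses up the regular attenders, leaving an intervention group enriched for new patients and a false quit-rate difference of several points. The documents do not support that. Depletion is small if few attenders are enrolled. Earlier decliners and missed patients remain available, so a group made up wholly of new patients is not a credible bound. The exclusion rule also works on the control side. For example, start from 30% new and 70% returning. Enrolling 40% of returning patients as controls leaves 30/(30 + 42) = 42% new in the later pool; excluding 40% of returning controls leaves 30/(30 + 42) = 42% new among controls, and the contrast vanishes. The low delivery of brief advice reported so far suggests few such exclusions to date, but does not settle the final balance. Nor does the article say whether the planned 11% effect is absolute, so expressing any bias as a share of it is unsafe.

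Finally, adjustment is incomplete. Among returning patients, it would still compare regulars who enrolled as controls with regulars who had declined or been missed.

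**Conclusion.** The point holds in limited form. The article's own rules bar every former control from the intervention group, the recruitment windows are unequal, and no measure of attendance before enrolment is named for collection or adjustment. An imbalance in new and returning patients is therefore possible, chiefly in the ambulatory clinics. This is relevant now: of the five sites that have started SBIR, four are ambulatory.

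The size and net direction are not established. The range of -5 to +39 points in new-patient share rests on assumed visit intervals, new-patient fractions, enrolment and exclusion rates, and no bias in an outcome can be quoted from the documents. The case for a change does not depend on the sign, since measuring prior attendance shows an imbalance in either direction and lets the models reduce it.

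**What to change.** Extend the planned administrative and Connect Care extraction backward from enrolment, for example by 12 months or more where available. Sites had to have used Connect Care for at least 6 months before joining, so a 6-month look-back should exist even for the first controls. Use the same look-back length in both groups. Six months alone would label annual attenders as new, so the longer window is preferable.

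For every participant, derive prior attendance at the recruiting unit and prior hospital and emergency use. Report these by group, add them to the behaviour and utilization models, and present a new/returning breakdown for the ambulatory clinics as a sensitivity analysis. Name the variables before the extraction is requested; the article says analysis awaits complete data, so there is still time.

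The cost is slightly more data extraction and a few lines of analysis text. Some strata will be imprecise, with 175 intervention participants so far. Differences between enrolled regulars and earlier decliners or missed patients will remain and should be stated as a limitation.

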Cost-effectiveness analysis will document the economic value of the SBIR intervention in order to communicate that value to decision-makers. Cost reduction/avoidance within one year, attributable to SBIR, will be estimated based on the reduction in 1-year readmissions and emergency visits, compared to the non-intervention comparison group. Estimates of this economic impact will be provided by applying hospitalization and emergency visit cost data, provided by Canadian Institute of Health Information (CIHI), to the utilization estimates from the above-mentioned models. Intervention implementation cost data are being collected throughout the project.

*Ethical considerations:* This study has received ethics approval from the Health Research Ethics Board of Alberta – Community Health Committee- at the University of Calgary (HREBA.CHC-22-0058).

*Involvement of people with lived experience:* IPiC-Health project has 7 patient advisors, who closely work with the research and innovation team of IPiC-Health project. The patient advisors provide insights based on lived experience to inform SBIR pathways, the research and implementation plan, development of resources, brief conversation scripts, and provide advice on acceptability and appropriateness on all aspects of the research and intervention. The Patients advisors consist of individuals connected to the Alberta Strategy for Patient Oriented Research SUPPORT Unit (AbSPORU) and Patient and Community Engagement Research (PaCER) | University of Calgary-trained patient researchers who have lived experience of care in Alberta’s patient care settings and/or with the risk factors targeted by the SBIR intervention.

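### Prior admissions and emergency visits are not named as confounders for the one-year utilization models, and Table 1 plans no extraction before the index visit that would allow adjustment for them

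*Protocol article*

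**What the plan says.** In the section on effectiveness outcomes, the outcome is defined as: "Health care utilization measures include hospital readmissions and emergency visits within one year of the index discharge/visits". The healthcare resource use row of Table 1, which the text presents as the detailed data collection plan, gives the same window: "Hospital readmissions and emergency visits during the year after index hospitalization discharge /visit". That row also takes primary care visits within a year after the index event, and "diagnoses/comorbidities at the time of recruitment to 1-year of index hospitalization discharge/visit".

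The sources are "Administrative health databases: Discharge Abstract Database, National Ambulatory Care Reporting System, and physician claim databases", linked by personal health number. The text adds: "Diagnosis and comorbidity related variables will be obtained from the administrative health databases".

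The analysis paragraph plans competing-risk Cox models for health care use, "to compare outcomes between the two groups adjusting for confounders, such as reasons or diagnosis for visits/admissions, comorbidity, and socioeconomic status". Sociodemographic and socioeconomic variables come from the 6-month interview.

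The cost saving "will be estimated based on the reduction in 1-year readmissions and emergency visits, compared to the non-intervention comparison group". Unit costs are applied to the utilization estimates from these same models.

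The comparison group comes from the same units in the 6-month period before implementation. The intervention group consists of later patients who screened at increased risk and received brief intervention and referral support.

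**The concern.** How often a patient used hospital and emergency care in the recent past is likely to be a strong predictor of use in the following year. In a randomised comparison it would balance on average. Here the groups are formed in successive periods and by different routes. Controls are recruited and screened by research coordinators. Intervention patients must actually have received the intervention, and the section on implementation challenges lets providers judge for whom it is suitable. If frequent users are more or less likely to be judged suitable, prior use will differ between the groups for reasons unrelated to any effect of SBIR.

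Diagnosis and comorbidity will carry part of this information but need not separate a frequent user from a one-time user with the same conditions. Residual imbalance would show up as visits avoided or added. The cost analysis would then turn it into money, in an evaluation that the article says is meant to support decisions on spread and scale.

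**Working it through.** **Step 1: what could be adjusted for under the stated extraction.** Taking the Table 1 row item by item:

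- Readmissions and emergency visits: the year after the index event.
- Primary care visits: within one year after the index event.
- Diagnoses and comorbidities: from recruitment to one year after the index event.
- Prior admissions or emergency visits: not listed.

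The covariates in the behaviour-change row of Table 1 (sociodemographic, socioeconomic, physical and mental health status) do not include prior use either. The confounder list in the analysis paragraph is open, so a fuller analysis plan could name prior use. It could not compute it from data that start at the index visit. The gap therefore lies in the extraction window as well as in the covariate list.

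**Step 2: how large the effect could be.** The documents give no event rate, no share of prior users and no figure for the utilization outcomes; the sample size rests on tobacco quitting. There is thus no stated figure to reproduce. All inputs below are assumptions:

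- R: event rate in prior users relative to other patients, 2 to 3.
- p_c and p_i: share of prior users among control and intervention patients.
- True SBIR hazard ratio: 1.
- No other covariate adjusted.

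Ratio under no effect = [1 + p_i(R − 1)] / [1 + p_c(R − 1)].

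| p_c | p_i | R = 2 | R = 3 |
|---|---|---|---|
| 0.40 | 0.30 | 1.30/1.40 = 0.929 | 1.60/1.80 = 0.889 |
| 0.40 | 0.35 | 1.35/1.40 = 0.964 | 1.70/1.80 = 0.944 |
| 0.30 | 0.40 | 1.40/1.30 = 1.077 | 1.80/1.60 = 1.125 |

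**Step 3: absolute scale.** This matters because the cost estimate uses it. With an assumed rate of 0.25 events per year in patients without prior use, the 40% v 30% mix gives:

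- R = 2: 0.25 × (1.40 − 1.30) = 0.025, or 25 apparent events avoided per 1,000 patient-years.
- R = 3: 0.25 × (1.80 − 1.60) = 0.050, or 50 per 1,000 patient-years.

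With the mix reversed, the same numbers appear as events added and would hide a true benefit of that size. In this simple model, full adjustment for prior use returns a ratio of 1.

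**The case against.** The strongest objection is that this is a condensed article, and a full covariate list with look-back periods usually belongs in the analysis plan or data request. The confounders are introduced as examples, so a reader who infers that the models will not adjust for prior use goes further than the text. That objection stands against such wording. It does not dispose of the point, because Table 1 states windows, and each starts at recruitment or the index event.

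Second, imbalance is not demonstrated. Both groups come from the same units and must screen at increased risk, and the named adjusters (reason for visit, diagnosis, comorbidity) probably share information with prior use. This also stands. A reader might infer that prior-use differences are carried into the SBIR effect, or that 7 to 11% (1 − 0.929 and 1 − 0.889) is the plan's bias. The documents support neither: those figures come from assumed inputs in an unadjusted comparison.

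Third, the pre-post label might be read as promising each patient's own utilization before the index visit. It does not. The section defines the design as patients from the implementation period against patients from the period before it, so there is no contradiction.

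Finally, one might expect adjustment to narrow the confidence interval as well. The familiar gain from a correlated baseline is a linear-model result. It does not carry over to the log hazard ratio in the planned Cox-type models, so the case rests on bias control alone.

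**Conclusion.** The point holds in limited form. Prior service use is not named as a confounder, and no extraction before the index visit is described, so an analysis working from the stated data could not adjust for it. Because the comparison is non-randomised and non-concurrent, with provider judgement influencing who is treated, a difference in prior use may confound the utilization hazard ratios and the cost saving derived from them.

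Neither size nor direction can be established from the documents. The ratios of 0.93 to 0.89 depend on a 10-point difference in prior users, a two- to threefold event rate and no help from the other covariates. A 5-point difference gives 0.96 to 0.94, and reversing the 10-point difference gives 1.08 to 1.13. This is a cheap improvement to bias control that is worth making; it does not show that the planned result is wrong.

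**What to change.** Extend the planned administrative extraction to the 12 months before the index date for both groups, excluding the index stay. Name the prior-year counts of hospital admissions and of emergency visits as covariates in each utilization model, and carry the adjusted estimates into the cost analysis.

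The article describes the administrative data as still to be obtained, so the change amounts to a longer date range in the same linkage, two more covariates and possibly a small data-access or ethics amendment. It needs no patient contact and does not depend on the 6-month interview, to which about half of patients respond.

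Three limits should be recorded:

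- That the databases hold records from before the index date is a reasonable inference from their being routinely collected, but the article does not say so; the custodian should confirm it.
- Patients who moved to Alberta within the prior year will have incomplete look-back.
- The exclusion of controls who later return and receive SBIR acts on use after recruitment, so adjustment for prior use would address it only in part.
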